
### Sample size

This is the first study examining the effects of sLORETA ISF-NFB in an ID population. Due to its novelty, there was no existing information around standard deviations for the measurements of interest. Therefore, no formal sample size or power calculations were made. Our group has previously carried out an sLORETA ISF-NFB trial in obese females [159]; however, this is a different population than the one in our trial and therefore not considered comparable for this study. Importantly, due to the pilot nature of this trial, only potential efficacy (or lack thereof) can be established via statistical analyses.

### Statistical considerations

#### Objective 1

Between-group (sham vs. ISF1 and ISF2) comparisons post-6 sessions will be performed for the PROs and neurophysiological measures. For this analysis, we will use LORETA-Key software and a Bayesian model with random effects to allow for baseline differences and non-specific temporal effects between participants. A sensitivity analysis will be carried out to compare this approach with an ANCOVA that includes a linear baseline adjustment.

#### Objective 2

Regression methods will be used to explore the relationship between changes in the primary PRO subscales (i.e. HADS-A, HADS-D) and targeted ROI activity and connectivity for all participants post 6 sessions.

#### Objective 3

Within-group (ISF1 and ISF2) comparisons between post-6 sessions and post-12 sessions will be performed for all outcome measures. The same model will be applied as in Objective 1 where random effects will now allow for post-6 session differences between participants.

#### Objective 4

Within-group (ISF1 and ISF2) comparisons between post-12 sessions and 1-month follow-up will be performed for all outcome measures. This will use the same model as Objective 1 where random effects will now allow for post 12-session differences between participants.

#### Objective 5

Regression analysis from Objective 2 will be extended to post 12-session and 1-month follow-up for the ISF1 and ISF2 groups.

Analyses were performed using LORETA-KEY software, R, JAGS [299] and Stan [300] with analysis-specific details described below. For all endpoints, responses were modelled assuming a normal distribution (e.g. with group-specific means and variances or via regression). When normality assumptions were not met, appropriate transformations were performed. Additionally, potential endpoint covariates were examined (e.g. age); however, none exhibited correlations that were strong enough to warrant inclusion for denoising purposes in the models. For the Bayesian analysis, JAGS or Stan was linked to R using the rjags or rstanarm library with estimates based on 3 chains of 25,000 iterations with a burn-in/warm-up = 10,000 iterations. Vague priors were used throughout.

Bayes’ theorem postulates that the probability of an event A given event B is proportional to the probability of event B given event A multiplied by the prior probability of event A:$$P\left(A|B\right)\propto P\left(B|A\right)\ast P(A)$$

Bayesian statistical analysis is based on the concept of prior knowledge/beliefs regarding random variables P(A) that are combined with a model relating data to those variables P(B|A) to generate a posterior probability distribution reflecting updated knowledge/beliefs about the variables given the collected data P(A|B) [301].

The describe_posterior() function in the BayestestR package [302] was used to generate posterior summary statistics including the distribution mean (*M*), 95% credible interval (i.e. highest density interval, HDI), probability of direction (pd), and the percentage of the full posterior within the region-of-practical-equivalence (% in ROPE).The HDI is the range of parameter values with a higher probability density than values outside the HDI [303]. As such, a 95% HDI can be interpreted as a 95% probability that the true (unknown) estimate lies within the interval, given the observed data and priors [304]. In other words, it is an index of the top 95% most credible parameter values.The pd is an index of the *existence* of an effect and is represented by the certainty (50-100%) in the direction, positive or negative [302, 305]. Put simply, it is the percentage of the posterior on the same side as the posterior’s measure of central tendency (e.g. the mean). For pd interpretation, the following reference values have been suggested:≤95% = uncertain>95% = possibly existing>97% = likely existing>99% = probably existing>99.9% = certainly existingThe percentage in ROPE indexes the *magnitude* of an effect where the ROPE is the range of effect size values considered to be practically equivalent to the null [302, 305]. There is no uniquely correct ROPE; however, by convention, the ROPE range is often set at half the size of Cohen’s definition of small effect size (i.e. 0.2 [306];) resulting in ROPE values of ±0.1 and ±0.05 for *standardized* mean differences (e.g. Cohen’s *d* = group 1 mean – group 2 mean/pooled standard deviation) and *standardized* regression coefficients (i.e. sβ = coefficient from a regression on standardized variables), respectively [303]. As an aside, Cohen’s *d* values can be interpreted as follows: *d* < ±0.10 = negligible, ±0.10 < *d* < ±0.20 = very small, ±0.20 < *d* < ±0.50 = small, ±0.50 < *d* < ±0.80 = medium, and *d* > ±0.80 = large [306] whereas sβs can be interpreted as follows: sβ < ±0.20 = weak association, ±0.20 < sβ < ±0.50 = moderate association, sβ > ±0.50 = strong association [307]. For percentage in ROPE interpretation, the following reference values have been suggested:>99% = negligible>97.5% = probably negligible≤97.5 and ≥2.5% = undecided<2.5% = probably significant<1% = significant

For all outputs, checks for the validity of assumptions regarding the residuals (i.e. normal distribution, constant and equal variances), chain convergence (e.g. trace plots), and posterior predictive model fit (e.g. Bayesian *p*-value) will be performed. Of note, a Bayesian *p*-value can be defined as “the probability, given the data, that a future observation is more extreme (as measured by some test variable) than the data” with values near 0.5 indicative of good model fit [308].

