**Methods:**

We will randomly assign participants who meet the criteria for MDD, GAD, and/or SOC per the MINI (Mini International Neuropsychiatric Interview for DSM-5) to one of three groups: (1) 12 sessions of posterior cingulate cortex (PCC) ISF-NFB up-training (*n*=15), (2) 12 sessions of concurrent PCC ISF up-training and dorsal anterior cingulate cortex (dACC) ISF-NFB down-training (*n*=15), or (3) 6 sessions of yoked-sham training followed by 6 sessions genuine ISF-NFB (*n*=30). Transdiagnostic PROs (Hospital Anxiety and Depression Scale, HADS; Inventory of Depression and Anxiety Symptoms – Second Version, IDAS-II; Multidimensional Emotional Disorder Inventory, MEDI; Intolerance of Uncertainty Scale – Short Form, IUS-12; Repetitive Thinking Questionnaire, RTQ-10) as well as resting-state neurophysiological measures (full-band EEG and ECG) will be collected from all subjects during two baseline sessions (approximately 1 week apart) then at post 6 sessions, post 12 sessions, and follow-up (1 month later). We will employ Bayesian methods in R and advanced source-localisation software (i.e. exact low-resolution brain electromagnetic tomography; eLORETA) in our analysis.

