#### Secondary research questions

##### Objective 3

To assess the potential clinical effects of an additional 6 treatment sessions (i.e. post-6 to post-12 sessions), we will examine changes in PROs and neurophysiological measures amongst the ISF1 and ISF2 groups. We hypothesize that additional sessions will provide additional benefits for both treatment groups.

##### Objective 4

To explore the potential for increased medium-term effects from ISF-NFB treatment at 1-month follow-up, we will examine changes in PROs and neurophysiological measures amongst the ISF1 and ISF2 groups.

##### Objective 5

To explore whether any potential associations observed in Objective 2 can be extended to post 12 sessions and 1-month follow-up amongst the ISF1 and ISF2 groups.

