### Randomization

Following baseline #2 measurements, participants were randomized to one of 3 arms: (1) yoked-sham, (2) ISF1 = PCC up-training, or (3) ISF2 = concurrent PCC up-training and dACC down-training. Sham participants were offered active ISF-NFB upon their completion of the trial, thereby minimizing the potential of sham trial-associated participation barriers [202] as well as addressing any potential ethical concerns of sham-only allocations.

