### Procedure for unblinding if needed

Treatment assignment will be disclosed to trial participants only upon their completion of the study.

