### Participant timeline

The trial period for each participant will be approximately 10 weeks and consist of one 30-min screening interview, two 60-min baseline assessments approximately 1 week apart, six 30-min genuine or sham ISF-NFB sessions (3× per week over 2 consecutive weeks) starting within 1 week after baseline #2, a 60-min post 6 sessions assessment, six 30-min genuine ISF-NFB sessions (3× per week over 2 consecutive weeks), a 60-min post 12 sessions assessment, and a 60 min 1-month follow-up assessment (Table 2 and Fig. 2). All post-treatment assessments and procedures will be identical to those performed at baseline.

**Table 2 Tab2:** Schedule of enrollment, interventions, and assessments

	T0	T1	T2	Allocation	T3-8	T9	T10-15	T16	T17
Enrollment									
Eligibility screen (MINI)	✓								
Informed consent	✓								
Anthropometric measures	✓								
Assessments									
PROs		✓	✓			✓		✓	✓
EEG		✓	✓			✓		✓	✓
ECG		✓	✓			✓		✓	✓
DESS					✓		✓	✓	✓
Blinding integrity						✓			
Groups									
Active	✓	✓	✓	✓	✓	✓	✓	✓	✓
Sham	✓	✓	✓	✓	✓	✓			

*Abbreviations*: *MINI* Miniature International Neuropsychiatric Interview, *PROs* patient-reported outcomes, *EEG* electroencephalography, *ECG* electrocardiography, *T0* interview, *T1* baseline #1, *T2* baseline #2, *T3–8* neurofeedback sessions 1 through 6, *T9* post 6^th^ session assessments, *T10–15* neurofeedback sessions 7 through 12, *T16* post 12^th^ session assessments, *T17* 1-month follow-up assessments

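### The schedule for the 30 sham-first participants after the post-6 assessment is contradictory, and Objective 3's benefit hypothesis rests on uncontrolled within-arm change

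*Protocol article*

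**What the plan says.** **Schedule.** The abstract (Methods) defines the third arm, n=30, as "6 sessions of yoked-sham training followed by 6 sessions genuine ISF-NFB". It adds that outcome data "will be collected from all subjects during two baseline sessions (approximately 1 week apart) then at post 6 sessions, post 12 sessions, and follow-up". The Participant timeline text agrees: "The trial period for each participant will be approximately 10 weeks", and that period includes "six 30-min genuine ISF-NFB sessions (3× per week over 2 consecutive weeks), a 60-min post 12 sessions assessment" and a 1-month follow-up, with no exception for the sham arm. Intervention descriptions likewise gives participants 12 sessions in total.

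The Randomization section says otherwise: "Sham participants were offered active ISF-NFB upon their completion of the trial". In Table 2 the Sham row is ticked up to T9 (the post-6 assessment) and blank at T10–15, T16 (post-12) and T17 (1-month follow-up), whereas the Active row is ticked throughout. The unblinding section adds: "Treatment assignment will be disclosed to trial participants only upon their completion of the study".

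**Objective 3.** Secondary research questions states: "We hypothesize that additional sessions will provide additional benefits for both treatment groups". The analysis under Statistical considerations is: "Within-group (ISF1 and ISF2) comparisons between post-6 sessions and post-12 sessions will be performed for all outcome measures". It reuses the Objective 1 model, with participant random effects now taken from post-6. Objective 4 is handled the same way from post-12 to follow-up, but carries no benefit hypothesis.

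**The concern.** The schedule determines whether any randomised comparison with the sham-first arm exists after T9. It also determines when 30 participants may learn their allocation, since disclosure is tied to completing the study: after T9 on one reading, after T17 on the other. ISF1 versus ISF2 stays randomised under either schedule, but both arms receive the same number of sessions, so that comparison says nothing about the value of extra ones.

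Objective 3 asks a causal question about sessions 7–12, and its analysis has no comparator. Objective 1 itself expects every group to improve through non-specific effects. If some of that improvement continues after session 6, the planned analysis will count it as benefit from the additional sessions.

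**Working it through.** **1. The schedule, source by source, for the sham-first arm after T9**

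| Source | Genuine sessions 7–12 in the trial? | Assessed at T16 and T17? |
|---|---|---|
| Abstract, Methods | Yes | Yes, all subjects |
| Participant timeline, text | Yes, each participant | Yes |
| Randomization | No, offered on completing the trial | Not stated |
| Table 2, Sham row | Blank | Blank |

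The allocation reproduces: 60 × 2/4 = 30 and 60 × 1/4 = 15 for each active arm. The conflict therefore covers 30 of 60 participants.

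Table 2 alone could be read as showing only that the sham condition ends at T9. The Randomization section closes that route, because genuine sessions cannot be both part of the trial and offered after it. If completing the trial is taken to mean T9, the abstract and the timeline text are wrong to assess everyone at T16 and T17. No reading fits all four places.

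**2. What the Objective 3 model can separate**

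Write the mean post-6 to post-12 change in an arm as (effect of sessions 7–12) + (drift shared by the arm). The within-arm contrast estimates the sum. Participant random effects describe how individuals differ from the arm mean; they do not remove a shift in the mean itself. The duplicate baselines deal with regression to the mean before training starts and give no information on drift after post-6.

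**3. Illustration of size**

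The document gives neither a drift nor a correlation between visits, so both are assumed. True effect of sessions 7–12 = 0. Units are outcome SDs.

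- SD of change = √(2(1 − ρ)). At ρ = 0.7 this is √0.6 = 0.775.
- SE = 0.775/√15 = 0.200. At ρ = 0.6 and 0.8 the SE is 0.231 and 0.163.
- With a vague prior the posterior is approximately mean + SE × t with n − 1 df. Probability of direction (pd) above 95% for benefit then means t above its 95th percentile (1.761 on 14 df). Its frequency comes from a noncentral t with noncentrality drift/SE: 1.0, 1.5 and 2.0 for drifts of 0.2, 0.3 and 0.4.
- The second criterion also requires less than 2.5% of the posterior in the ROPE of ±0.1 (simulated, 400,000 draws).

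| Setting | Criterion | Drift 0 | 0.2 | 0.3 | 0.4 |
|---|---|---|---|---|---|
| n=15, ρ=0.7 | pd >95% | 5% | 24% | 41% | 60% |
| n=15, ρ=0.7 | pd >95% and ROPE <2.5% | about 1% | 8% | 17% | 31% |
| n=15, ρ=0.6 to 0.8 | pd >95% | 5% | 21–32% | 34–54% | 50–75% |
| n=15, ρ=0.6 to 0.8 | both | about 1% | 7–9% | 14–22% | 26–42% |
| n=13, ρ=0.7 | pd >95% | 5% | 22% | 37% | 54% |
| n=13, ρ=0.7 | both | 1% | 7% | 16% | 28% |

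The n=13 rows reflect the upper end of the expected 10–15% loss: 15 × 0.85 = 12.75. Statistical considerations reports both indices and does not say which one decides.

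**The case against.** The strongest reply concerns weight. The schedule conflict changes no planned estimate: Objectives 3–5 use only ISF1 and ISF2, and no sham-first comparison after T9 was ever proposed. The abstract calls the additional-session question exploratory, Objective 3 speaks of potential effects, the Sample size section limits the pilot to potential efficacy, and the analysis is openly labelled within-group. On this view the excess is one hypothesis sentence. The flow chart (Fig. 2), not reproduced in the text reviewed, might also show the path after T9.

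The headline frequencies use the lowest tier of the pd scale, which the protocol describes only as possibly existing. At pd >99%, with n=15 and ρ=0.7, the figures fall to 8%, 17% and 30%; adding ROPE <1% brings them to about 3%, 9% and 18%. Finally, a T16 contrast with the sham-first arm would not isolate sessions 7–12.

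Most of this stands as a limit on severity. It does not remove the point. A figure cannot reconcile statements in the text that exclude each other. The stricter criteria still exceed their no-drift rates (1% for pd >99%, about 0.3% for the pair) several times over. The hypothesis also asserts that extra sessions will help, and the exploratory label does not supply the comparator needed to examine that.

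**Conclusion.** The concern holds on both counts and should be fixed. The contradiction covers 30 of 60 participants and rests on the text alone. The limit on Objective 3 follows from the design: improvement from post-6 to post-12 within an arm cannot be credited to the extra sessions. The same limit applies to Objective 4.

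The size of the second problem is illustrative. It depends on assumed drifts of 0.2–0.4 SD and correlations of 0.6–0.8, and on which posterior index is taken as decisive. The document cannot show whether drift continues after post-6, and the design cannot check it. The primary post-6 comparison with sham is unaffected, and the planned estimates for Objectives 3–5 are the same under either schedule. What changes is the conclusion that they can support.

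**What to change.** - State one schedule for the sham-first arm after T9, and bring the abstract, Randomization, Participant timeline and Table 2 into line with it. This also settles when those participants may be unblinded.
- Present Objectives 3 and 4 as exploratory, uncontrolled change over time, and drop the hypothesis that additional sessions provide additional benefit.
- If the sham-first arm is assessed at T16, add a baseline-adjusted randomised contrast of ISF1 and ISF2 with that arm. Label it 12 versus 6 genuine sessions, or early versus delayed start. It should not be described as the increment from sessions 7–12, because the Background allows that effects may grow after training stops.
- If that arm is not assessed at T16, say plainly that T16 and T17 have no sham or delayed-start control.

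The cost is protocol wording, plus one further contrast from the same model if the T16 data exist. The price is a weaker claim for Objectives 3 and 4, and even the added contrast does not isolate the second block of sessions.

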### Trial design

This study is a randomized, double-blind (participants and assessors), yoked-sham controlled (playbacks of genuine ISF-NFB sessions from another female ID participant at the same training stage), parallel-group (3-arm = sham, ISF-1, ISF-2), superiority, pilot trial with an allocation ratio of 2:1:1 (sham:ISF1:ISF2).

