##### Hospital anxiety depressions scale (HADS)

The HADS is a valid and reliable 14-item, trans-diagnostic PRO measure used to assess anxiety and depression severities [218]. Response options are on a 4-point scale (0–3) based on participants experiences over the past week with anxiety and depression subscale scores graded as follows: 0–7 = ‘normal’, 8–10 = ‘mild’, 11–14 = ‘moderate’, and 15–21 = ‘severe’ [220]. The HADS has been repeatedly shown to be a reliable and valid tool across a variety of settings [219, 221, 222]. There is some debate with respect to whether the HADS is best assessed via the total 14-item score [223–225] or two 7-item subscale (anxiety and depression) scores [219, 222, 225, 226]. For our trial, we are considering the anxiety (HADS-A) and depression (HADS-D) subscale scores separately. Importantly, the minimum clinically important difference (MCID) for the HADS subscales is estimated to be a reduction of 1.5 to 2 points [227–229].

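### The ±0.1 SD ROPE cannot return a 'negligible' verdict at 15 versus 30 and ignores the cited HADS MCID, so potential lack of efficacy cannot be shown on this index

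*Protocol article*

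**What the plan says.** Under Statistical considerations, the article assigns the existence of an effect to the probability of direction and its magnitude to the percentage of the posterior in the ROPE. On the width it says that "by convention, the ROPE range is often set at half the size of Cohen’s definition of small effect size", "resulting in ROPE values of ±0.1 and ±0.05 for" standardised mean differences and standardised slopes respectively. It adds that no ROPE is uniquely correct, but gives no other. The suggested reference bands run, from the top, "99% = negligible>97.5% = probably negligible≤97.5 and ≥2.5% = undecided" (the first figure is a greater-than bound), then below 2.5% *probably significant* and below 1% *significant*. The same section states that vague priors were used throughout.

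The HADS section says that "the minimum clinically important difference (MCID) for the HADS subscales is estimated to be a reduction of 1.5 to 2 points". No analysis section refers to this figure again.

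The Sample size section reports no power calculation and no usable standard deviations. It closes with a pilot caveat that "only potential efficacy (or lack thereof) can be established via statistical analyses".

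**The concern.** An equivalence region is informative only if the posterior can be narrow enough to fit inside it. With arms of 15, 15 and 30 and vague priors, the posterior for a standardised difference is far wider than ±0.1. If the *negligible* bands are out of reach whatever the data, the index can report an effect or indecision but never absence of an effect, and the article does not say so. A reader could take *undecided* as a weak negative finding. In the other direction, a small observed share in a ±0.1 SD region could be read as clinical importance, although the region is not tied to the HADS points in which the article itself expresses clinical importance.

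**Working it through.** **Inputs from the article.** ROPE ±0.1 for d and ±0.05 for standardised slopes; bands at 97.5%, 99%, 2.5% and 1%; vague priors (Statistical considerations). Arms 15, 15 and 30 (Methods in the abstract; 2:1:1 in Trial design). HADS subscale MCID 1.5 to 2 points (HADS section). Expected loss 10–15% with complete-case analysis (section on non-adherence and missing data).

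**Assumptions.** Normal posterior equal to the likelihood. Baseline adjustment shrinks the standard error by √(1 − ρ²), where ρ is the baseline correlation and d is scaled by the unadjusted SD. HADS subscale SD of 3 to 4 points; the article gives none.

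**The plan's own figure.** Half of a small effect: 0.2/2 = 0.1. This reproduces.

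**Best case for *negligible*: observed difference exactly zero.**
- Posterior SD at 15 versus 30: √(1/15 + 1/30) = √0.1 = 0.316.
- Share in ROPE: 2Φ(0.1/0.316) − 1 = 24.8% (24.7% with a t reference).
- ρ = 0.6: SD 0.316 × 0.8 = 0.253, share 31%. ρ = 0.9: SD 0.138, share 53%.
- After losses, 13 versus 26: SD √(1/13 + 1/26) = 0.340, share 23%.
- Both active arms pooled, 30 versus 30: SD √(2/30) = 0.258, share 30%.
- Standardised slope, n = 60 (Objective 2): SD about 1/√58 = 0.131, share in ±0.05 is 2Φ(0.05/0.131) − 1 ≈ 30%.

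**What 97.5% would need.** 0.1/SE = z(0.9875) = 2.241, so SE = 0.0446. With n active and 2n sham, SE² = 1.5/n, so n = 1.5/0.0446² ≈ 754 active and 1,508 sham. At 15 versus 30 it would need ρ of about 0.99.

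**The other end, unadjusted.** Solve Φ((0.1 − d)/0.316) − Φ((−0.1 − d)/0.316) for the band limit, then take P(benefit < 1.5 points) = Φ((1.5/SD − d)/0.316).

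| Band | Observed d needed | SD 3 | SD 4 |
|---|---|---|---|
| <2.5%, *probably significant* | 0.69 | 28% | 16% |
| <1%, *significant* | 0.81 | 16% | 8% |

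A two-sided 5% test needs d = 1.96 × 0.316 = 0.62. On the HADS scale ±0.1 SD is ±0.3 to ±0.4 points, against an MCID of 1.5 to 2.

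**Would a ±1.5 point ROPE cure it?** At a zero difference its share is 2Φ((1.5/SD)/SE) − 1. Unadjusted, that is 89% (SD 3) and 76% (SD 4); at ρ = 0.6 it is 95% and 86%. To have less than 2.5% inside it, the observed difference must be about 3.4 to 4.0 points unadjusted, or 3.0 to 3.5 at ρ = 0.6.

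**The case against.** The Sample size sentence is a limiting one. It opens by appealing to the pilot nature of the trial and speaks only of potential efficacy. A reader might infer that the article promises to prove the treatment ineffective and so contradicts itself; the text does not go that far. What stands is that it still says a potential lack of efficacy can be established, and the magnitude index cannot deliver that.

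The bands are described as suggested reference values, and no section ties a trial conclusion to one. *Undecided* is also the right answer for a null result in a small pilot, and a rule that cannot declare negligibility cannot do so falsely. Both points are fair and limit the weight of the finding. They do not remove it: these bands are the only reading given for the index, and readers are not told that one end is closed.

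The posterior mean, the HDI and the probability of direction are already planned, so a reader could judge clinical size if the HDI is given in points. That is also fair, and it leaves the MCID-based probabilities as the only new summaries.

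It is tempting to conclude that the ROPE must be reset to ±1.5 points. The documents do not support that. The MCID is described as a reduction in score, not as a between-group margin below which differences are practically null. As the working shows, the wider region would still miss 97.5% at the assumed SDs unless baseline correlation is high, and it would push the *probably significant* band to roughly twice the MCID.

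**Conclusion.** The point holds in limited form. With vague priors and 15 versus 30, at most about 25% of the posterior can lie in the ±0.1 ROPE (31% at an assumed ρ of 0.6, 53% at 0.9), and about 30% in the ±0.05 slope ROPE at n = 60. The index can therefore return *undecided* or one of the two *significant* bands, never a *negligible* one. This does not depend on the unknown HADS SD and applies to the other endpoints read on the same scale. The clinical-size part concerns HADS only and rests on the assumed SD of 3 to 4: the 28–16% chance of a benefit below 1.5 points belongs to the *probably significant* band, and the stricter *significant* band gives 16–8%. This is a matter of interpretation and wording that should be corrected. It does not invalidate the model or the design.

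**What to change.** 1. For HADS-A and HADS-D, report the posterior between-group difference in points with its 95% HDI, and add P(benefit ≥ 1.5) and P(benefit ≥ 2). State that the cited MCID is being applied to a between-group difference.
2. In the Sample size section, delete the parenthesis on lack of efficacy, or add that at 15 versus 30 an *undecided* result is not evidence of no effect.
3. For all endpoints, drop the *negligible* labels or note that they cannot be reached at this sample size.

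The conventional ROPE may stay as a descriptive summary. The cost is two more posterior summaries per HADS subscale, taken from draws already generated, and a slightly less favourable stated conclusion. No new data or participants are needed.
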